**7.2 Indicators of safety evaluation**

The indicators of safety evaluation of this study include:

- Incidence, severity and serious adverse events of chemotherapy-related adverse events, refer to NCI CTCAE v4.03 criteria;
- Incidence and severity of operation-related complications (perioperative mortality, intraoperative bleeding/transfusion, postoperative blood transfusion and number of blood units used), incidence and severity of systemic complications and local liver complications. Evaluation is completed at 48 hours, 1 month, and 3 months postoperatively using the assessment criteria of Clavien-Dindo grading scale system.

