In summary, compared with the traditional doublet (FOLFOX/FOLFIRI/XELOX) treatment, the triplet or doublet treatment plus cetuximab can further improve the ORR of chemotherapy and improve the resection rate of liver metastases. Logically, some researchers propose that triplet regimen plus cetuximab may achieve higher ORR. Assenat et al. conducted a phase Ⅱ single-arm study to investigate the efficacy of cetuximab plus FOLFOXIRI (CPT-11 180 mg/m^2^) in advanced CRC. The results showed that for KRAS wild-type patients, the overall ORR was 83.3%, and PFS and OS were 9.5 and 24.7 months, respectively [11]. The study by Folprecht et al. further explored the safety and the response rate of the combination of cetuximab and triplet regimen in first-line treatment of advanced CRC. The results showed that the ORR of the quadruplet regimen was 75%, with Grade 3/4 adverse events including diarrhea (25%), agranulocytosis (40%), and rash (15%) [12]. In another single-arm study reported by Antoniotti et al. (GONO MACBETH), the ORR of cetuximab plus triplet (CPT-11 130 mg/m^2^) regimen was 71.6%, and the R0 surgical resection rate was 50% in patients with liver metastases only [13]. Geissler et al. further reported a study (VOLFI) of cetuximab plus triplet regimen versus triplet regimen for first-line treatment of advanced CRC. The study results showed that the ORR of the quadruplet regimen of cetuximab plus triplet (CPT-11 150 mg/m^2^) versus triplet regimen were 85.7% and 60.6%, respectively, and the R0 surgical resection rates of metastatic lesions in subgroup analysis were 50% vs. 27.3%, respectively.

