### 2.2 Secondary objectives

- Depth of response (DpR)
- R0/resection rate
- Early tumor shrinkage (ETS)
- Progression-free survival (PFS) of the whole group
- OS in the whole group
- Safety (adverse reactions of chemotherapy, surgical complications, etc.)

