**6.4** **Management of adverse reactions due to cetuximab**

- Infusion-related reactions, including anaphylaxis

Severe infusion-related reactions, including anaphylaxis, can occur frequently and in some cases can be fatal. Once severe infusion reactions occur, discontinue the drug immediately and permanently and provide emergency treatment. Some of these reactions may be reported as anaphylaxis, anaphylactoid reactions or presented as cytokine release syndrome (CRS). Symptoms may occur during the first infusion and hours after the end of the infusion or in subsequent instillations. The physician is recommended to inform the patient of the possibility of delayed onset of this reaction and ask the patient to contact the physician immediately if symptoms occur. Possible symptoms include bronchospasm, urticaria, high or low blood pressure, loss of consciousness, or shock. Angina pectoris, myocardial infarction, or sudden cardiac arrest are rare.

Anaphylaxis may occur within minutes of the first infusion, e.g., caused by preformed IgE antibodies that cross-react with the drug. These reactions are usually accompanied by bronchospasm and urticaria. These reactions may occur despite premedication. Patients who are allergic to red meat or tick bites or who are positive for IgE antibodies to cetuximab (α-1-3-galactose) have much higher risk of anaphylaxis. For these patients, the risks and benefits, including alternative therapies, should be carefully assessed before application of the drug, and the drug can only be used under the close supervision of trained professionals equipped with resuscitation equipment.

The first dose should be administered slowly, the instillation rate should not exceed 5 mg/min, and all vital signs should be closely monitored for at least 2 hours. If an infusion-related reaction occurs within 15 minutes of the first dose, the instillation should be discontinued. Careful risk-benefit assessment should be performed before subsequent infusions, including consideration of whether the patient has preformed IgE antibodies.

If infusion-related reactions occur late in the instillation or in the subsequent instillations, the corresponding management depends on the severity of the reaction:

1. Grade 1: perform instillation continuously and slowly under close monitoring
2. Grade 2: perform instillation continuously and slowly and adopt symptomatic treatment immediately

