## 9. Assessment during the study

## 9.1 Pre-chemotherapy assessment

The following assessments will be performed during each course:

- Concomitant medication
- Clinical data: weight, physical examination, vital signs, ECOG performance score
- Laboratory tests: hematology, biochemistry (including ALP) and tumor markers on Day 0 and Day 14
- EKG
- Tumor assessment:

Assessments will be performed every 4 courses and the number of examinations may be increased if necessary.

Tumor measurements/assessments are performed using CT or MRI scans based on RECIST v1.1 criteria.

For each patient, the same assessment method should be used throughout the study, and the assessment should be performed by the same assessor as far as possible.

All metastases detected at baseline screening should be assessed at every tumor assessment.

- MDT assessment:

Every 4 courses, the number of assessments may be increased if necessary.

In this study, 8 (no less than 6) courses of conversion chemotherapy are recommended, and some patients also need to appropriately prolong the treatment course before hepatectomy with or without radiofrequency treatment is considered.

This is mainly because that this study includes patients with unresectable colorectal liver metastases, who usually have a large number of liver metastases, large lesions, with high-risk CRS score. Current clinical practice recommends surgical resection after adequate chemotherapy to achieve more benefit.

- Chemotherapy related adverse events
- Survival

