### 11.2 Scope of expected adverse events

Common adverse reactions:

- Digestive system: diarrhea, nausea, vomiting, abdominal pain, stomatitis, etc. Serious (Grade 3-4) gastrointestinal reactions are relatively rare.
- Blood: neutropenia, anemia, thrombocytopenia.
- Nervous system: headache, paresthesia, vertigo, insomnia, somnolence, etc.
- Skin: rash, exfoliation, etc.
- Others: alopecia, mucositis, pyrexia, weakness, fatigue, hypertension, thrombosis, liver and kidney function damage.

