### 11.4 Management of adverse events

**11.4.1 Recording of adverse events**

The investigator should explain to the patients and ask them to truthfully reflect the changes in their conditions after medication. Physicians should avoid asking leading questions. Any AEs occurring in the subjects during the trial, including laboratory abnormalities, must be carefully inquired and followed up. All AEs must be determined for its nature, severity and correlation with the drug. The investigator should follow up, observe and record the outcome of all AEs and follow up the patients who withdraw from the trial due to AEs until the AE is resolved. For each event, the following information should be recorded in the AE section of the CRF:

- Severity: Whether an AE is classified as SAE or non-SAE.
- AE: Whenever possible, the specific diagnosis of the event should be recorded. If a diagnosis is not possible, each sign or symptom should be recorded separately, e.g. nausea and vomiting are recorded as two AEs. If an event occurs several times and there is an appropriate time interval to explain that a subsequent condition can be considered a recurring symptom, each AE should be recorded separately on the CRF.
- Start date: The date the event started is recorded. If an abnormal laboratory change is reported as an AE, the date of collection of the first laboratory sample indicating a change in condition is recorded as the start date of the event. The start date of an SAE is defined as the date on which the event begins to meet the criteria for an SAE.
- End date: The date the event ended is recorded. If an abnormal laboratory change is reported as an AE, the collection date of the first post-hoc sample (for which detection can indicate that the condition returns to the pre-event status or returns to normal) is recorded as the end date of the event.
- Relationship to the investigational product
- Therapeutic Intervention: Any therapeutic intervention that is necessary is recorded in the concomitant therapy section of the CRF and noted as drug therapy or non-drug therapy.
- Outcome:

(1) Resolution of the event without sequelae - The patient recovers from the AE without any sequelae observed.

(2) Resolution of the event with sequelae - The patient has recovered from the AE but any sequelae is observed (specify sequelae in the AE section of the CRF).

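### Section 7.2 limits the adverse-event comparison to chemotherapy-related events, judged by investigators who know the arm, although all adverse events are already recorded

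*Protocol*

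**What the plan says.** - **Endpoint.** Protocol Section 7.2 gives the drug-safety indicator as "Incidence, severity and serious adverse events of chemotherapy-related adverse events, refer to NCI CTCAE v4.03 criteria". As worded, the restriction applies to serious events too. Section 2.2 likewise describes the safety objective in terms of adverse reactions to chemotherapy. No all-cause adverse-event indicator is named.
- **Visit schedule.** The list of assessments at each course in Section 9.1 has the item "Chemotherapy related adverse events".
- **Collection.** Section 11.4.1 is wider: "Any AEs occurring in the subjects during the trial, including laboratory abnormalities, must be carefully inquired and followed up". Each event is to be judged for nature, severity and relation to the drug. Section 11.1 says that the term adverse event implies no causal relationship.
- **Causality.** Section 11.3 lists five indicators and five categories, from definite to unrelated. It does not say which categories count as related for Section 7.2.
- **Blinding.** The Summary of Research Protocol describes an open-label trial. No blinded review of causality is described.
- **Surgical part.** Section 7.2 has a second indicator for operative, systemic and local liver complications, graded by Clavien-Dindo, with no drug attribution.
- **Expected events.** Section 11.2 states: "Serious (Grade 3-4) gastrointestinal reactions are relatively rare". Section 1 cites a study of cetuximab plus triplet with 25% Grade 3/4 diarrhea. Section 11.2 does not list infusion reactions, of which Section 6.4 says: "Severe infusion-related reactions, including anaphylaxis, can occur frequently and in some cases can be fatal".

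**The concern.** The trial has to weigh a gain in response rate against the toxicity of adding irinotecan. Randomization protects a comparison of everything that happens to patients in each arm. It does not protect a comparison of the part that an unblinded investigator attributes to chemotherapy. If the share of events called related differs by arm, the reported difference moves with no change in actual harm.

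Competing explanations are plentiful here. Patients may have liver resection, radiofrequency treatment, SBRT or rectal radiotherapy (Section 5.1) and hepatic arterial infusion (Section 5.2). Infection, liver dysfunction or thrombosis can plausibly be assigned to one of these or to the disease. Both arms receive cetuximab, so the added harm of the triplet is read most directly from the total event rate.

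The term is also not fully defined. Some text treats cetuximab as distinct from chemotherapy: postoperative treatment is chemotherapy with or without cetuximab (Section 5.2), and either may continue without the other (Section 6.1). Other text places it inside: Section 5.2 puts the cetuximab regimens under conversion chemotherapy, Section 6.4 sits within the chapter on chemotherapy dose adjustment, and Section 6.6 speaks of cetuximab chemotherapy.

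**Working it through.** The protocol states no figure for the safety comparison, so there is none to reproduce.

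**1. Passages side by side.** Collection covers all events (11.4.1), while the indicator covers chemotherapy-related events (7.2, 9.1). The filter between them is a causality judgement made without blinding. Data for an all-cause comparison are therefore required by the protocol, but that comparison is not the defined indicator.

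**2. How far could the filter move the result?** Let p be the proportion of patients with the event whatever the cause, and a the probability that such a patient is counted as having a related event, for triplet (T) and doublet (C).

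- Related difference = pT·aT − pC·aC
- Change from the all-cause difference = pC(1 − aC) − pT(1 − aT)

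Inputs: pT = 25% (Grade 3/4 diarrhea, Section 1). Assumed, not in the documents: pC from 5% to 15%, and a from 70% to 100% in each arm. A case with equal rates is added.

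| pT | pC | aT | aC | All-cause difference | Related difference |
|---|---|---|---|---|---|
| 25% | 5% | 0.8 | 1.0 | 20 points | 20 − 5 = 15 |
| 25% | 5% | 1.0 | 0.8 | 20 points | 25 − 4 = 21 |
| 25% | 5% | 0.8 | 0.8 | 20 points | 20 − 4 = 16 |
| 25% | 15% | 0.8 | 1.0 | 10 points | 20 − 15 = 5 |
| 25% | 15% | 1.0 | 0.8 | 10 points | 25 − 12 = 13 |
| 25% | 25% | 1.0 | 0.8 | 0 points | 25 − 20 = 5 |
| 25% | 25% | 0.8 | 1.0 | 0 points | 20 − 25 = −5 |

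Extremes over the assumed range:

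- Downward: aT = 0.70, aC = 1 gives −0.25 × 0.30 = −7.5 points.
- Upward: aT = 1, aC = 0.70, pC = 15% gives 0.15 × 0.30 = +4.5 points.

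**3. Patients with several events.** A patient counts if any event is called related. If each event is called related with probability 0.8, independently, then a = 1 − 0.2^k for k events: 0.80 for one, 0.96 for two, 0.992 for three. In the first row, with two events per triplet patient, the related difference is 0.25 × 0.96 − 0.05 = 19 points, not 15. The figures in step 2 are therefore toward the upper end. When judgements within a patient are correlated, the result lies between the two.

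**4. Section 11.2 against Section 1.** With 70 patients per arm (Section 4), 25% gives 70 × 0.25 = 17.5 triplet patients expected with Grade 3/4 diarrhea. The binomial probability of at least 10 is 0.990. That does not fit a description as relatively rare.

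**The case against.** The case on the other side is substantial, and several parts stand.

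- **No data are lost.** Section 6.1 has toxicity assessed before and at the end of each cycle, and Section 11.4.1 records all events. This stands; the defect lies in the indicator, not in collection.
- **The SAP may add all-cause tables.** It may: nothing in Section 7.2 forbids them, and Section 10.2 plans no specific test for adverse events, so the comparison is descriptive. But the protocol itself fixes the indicator as the attributed one, and a SAP leading with all-cause events would depart from that wording.
- **The magnitude is assumed.** This stands. Only the 25% is in the documents.

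Four stronger readings are tempting but not supported:

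- *That the expected-event list biases attribution.* Sections 11.2 and 11.3 do not refer to each other. The second causality indicator asks about the type of reaction, not its frequency, and diarrhea is on the list of common reactions.
- *That all safety counting is filtered.* The Clavien-Dindo indicator carries no drug attribution. For patients who have surgery, it covers infections and liver dysfunction.
- *That cetuximab reactions are excluded.* The protocol's usage is mixed, so this is an ambiguity only.
- *That Section 11.2 contradicts all the toxicity figures in Section 1.* It gives no frequency for severe neutropenia or rash, so the cited 40% agranulocytosis and 15% rash are not contradicted. The 25% comes from one cited study of the quadruplet and bears mainly on that arm.

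**Conclusion.** The point holds for the adverse-event part of Section 7.2. That indicator makes the toxicity comparison depend on unblinded attribution, with no stated cut-off for related and an unclear position for cetuximab. The possible distortion is a few percentage points either way under the assumptions shown. Neither its direction nor its actual size can be derived from the documents, and patients with several events reduce it. An all-cause comparison does not depend on those shares and uses data the protocol already requires. The primary endpoint and the surgical indicator are unaffected. The change should be made.

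The mismatch of Section 11.2 with Section 1 on severe diarrhea, and with Section 6.4 on infusion reactions, is a separate inconsistency. It has no shown effect on causality assessment.

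**What to change.** 1. In Section 7.2, make the main adverse-event comparison the incidence and worst CTCAE grade of all adverse events from first dose, and all SAEs, regardless of cause, by arm in the safety set.
2. Keep events related to any study drug (cetuximab or chemotherapy) as a second table, and state which of the five causality categories count as related.
3. Align the Section 9.1 item with Section 11.4.1, so that it covers all adverse events.
4. Separately, reconcile Section 11.2 with the 25% figure in Section 1 and with the account of infusion reactions in Section 6.4.

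Cost: wording and one more set of tables, with no new data collection. Stated adverse-event rates will be higher in both arms, because events not attributed to treatment are included.

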**8. Screening and baseline visit**

Patients should not undergo any screening procedures before signing the written informed consent. If any of the following procedures (such as tumor assessment) are completed as a routine clinical practice within the protocol-required time window before patients sign the written informed consent, they are not repeated if the investigator considers the results to be reasonable and acceptable. Only the data of eligible patients screened according to the inclusion and exclusion criteria can be filled in the case report form (CRF). All patients who sign the written informed consent form will be screened, and baseline screening will be performed from 28 days prior to initiation of study treatment to 24 hours prior to initiation of study treatment, including the following:

**Day -28 to -1**

- Signing of written informed consent form: date.
- Demographic characteristics: age, sex.
- Medical history: including gastrointestinal diseases, hypertension, thromboembolic diseases, cardiovascular diseases, renal diseases and other significant diseases.
- Cancer and treatment history: time of first treatment; initial diagnosis of CRC (date, lymph node status, TNM stage, histological tumor grade, primary tumor lesion [colon or rectum]); diagnosis of metastatic disease (date, metastases, CT scan [abdomen, chest, pelvis]); previous treatments (surgical resection of primary tumor, local radiotherapy); previous chemotherapy (regimen, type [adjuvant, neoadjuvant], time, course, dose).
- Concomitant medication: drugs possibly related to the occurrence of adverse events or related to the management of adverse events should be recorded.
- Physical examination: complete physical examination should include head, eyes, ears, nose, throat, cardiovascular, skin, muscles and bones, respiratory, digestive, genitourinary and nervous system; abnormalities observed at baseline should be recorded in the corresponding parts of the general medical history and baseline conditions in the CRF; at subsequent visits, local, symptom-oriented physical examination should be performed; abnormal signs with changes from baseline should be recorded in the patient’s notes; new or worsened abnormalities should be recorded as adverse events in the relevant parts of the adverse events in the CRF.
- Height and weight
- Vital signs: including measurements of pulse rate, sitting systolic/diastolic blood pressure, and body temperature.
- ECOG performance status score.
- ECG.
- Whole body CT scan + enhanced scan.
- FDG-PET: only perform when necessary; not mandatory.
- Liver MRI scan + enhanced scan, contrast agent enhancement with Primovist if available.
- Pelvic MRI scan + enhanced scan is recommended for patients with rectal cancer.
- Tumor assessment: assessed by the investigator based on RECIST 1.1 criteria.
- RAS and BRAF gene status (detection method not limited)

**Day -7 to -1**

- Laboratory tests (dates, values): hematology, biochemistry (including ALP), tumor markers
- Surgery assessment by MDT: resectability is determined based on the following given criteria for unresectability:
- Metastatic lesions ≥ 5
- Ineligible for R0 resection
- Expected insufficient residual liver volume after resection
- Unable to preserve all three hepatic veins after resection, unable to ensure that the blood flow and bile ducts of the residual liver into and out of the liver could be preserved, and unable to preserve the adjacent two liver segments.

Patients who meet any of the above criteria can be determined as having initially unresectable liver metastases.

## 9. Assessment during the study

## 9.1 Pre-chemotherapy assessment

The following assessments will be performed during each course:

- Concomitant medication
- Clinical data: weight, physical examination, vital signs, ECOG performance score
- Laboratory tests: hematology, biochemistry (including ALP) and tumor markers on Day 0 and Day 14
- EKG
- Tumor assessment:

Assessments will be performed every 4 courses and the number of examinations may be increased if necessary.

Tumor measurements/assessments are performed using CT or MRI scans based on RECIST v1.1 criteria.

For each patient, the same assessment method should be used throughout the study, and the assessment should be performed by the same assessor as far as possible.

All metastases detected at baseline screening should be assessed at every tumor assessment.

- MDT assessment:

Every 4 courses, the number of assessments may be increased if necessary.

In this study, 8 (no less than 6) courses of conversion chemotherapy are recommended, and some patients also need to appropriately prolong the treatment course before hepatectomy with or without radiofrequency treatment is considered.

This is mainly because that this study includes patients with unresectable colorectal liver metastases, who usually have a large number of liver metastases, large lesions, with high-risk CRS score. Current clinical practice recommends surgical resection after adequate chemotherapy to achieve more benefit.

- Chemotherapy related adverse events
- Survival

